### **Sample size**

Sample size calculation is based on change in weight. In a retrospective study from Sahlgrenska, mean (SD) reductions in BMI for super-obese patients 3 years after surgery were 24.9 (5.0) after duodenal switch (*n*=13) and 18.0 (6.7) after gastric bypass (*n*=19). Thus, 60 study participants would give >90% power to detect a difference in the change in BMI between groups (2-sided *t* test, *P*=.05).

Regarding quality of life, we expect that a 15% difference in score between the groups is clinically significant.

## **5. Practical considerations and responsibilities (Norwegian part of study)**

Patients are received at the obesity clinic at the first consultation at the hospital, and examined by a physician, research nurse and nutritionist.

The treating physician will clarify whether the patient is appropriate for the study and is responsible for informing the patient about the study, inviting for participation, and for obtaining signed informed consent. This doctor obtains appropriate blood tests, and is responsible for completing all forms including preoperative data.

The nutritionist will be responsible for informing and guiding the patient by filling in the questionnaires regarding quality of life and eating patterns. All participants receive standardized information about the postoperative diet.

Data regarding health economics are obtained from medical records (length of surgery, stay in recovery and intensive care, and total hospital stay). The responsible physician fills out these forms on the participant's departure.

At outpatient visits, data registration is performed by physician and nutritionist.

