## **2. Aims of the study**

To compare treatment outcome in super-obese (BMI 50-60), aged 20-50 years at inclusion, after:

- Laparoscopic gastric bypass with a long (150 cm) alimentary limb (long limb laparoscopic gastric bypass).
- Laparoscopic biliopancreatic diversion with duodenal switch (alimentary limb 200 cm and common channel 100 cm).

Primary end point: Long-term results regarding weight reduction and weight stability

Secondary end points: Long-term results regarding quality of eating and quality of life  
Per- and postoperative complications  
Postoperative mobilization and length of hospital stay  
Long-term complications (including surgical revisions)  
Changes in body composition  
Nutritional deficiencies after surgery  
Demand for hospital services (i.e. operating costs, outpatient visits)  
Long-term results regarding eating disorders  
Changes in comorbidities

Based on the same data set, more detailed studies regarding the nutritional consequences of surgery for obesity will be carried out. This is defined in more detail in a separate research protocol with the principal research fellow [name] and professor [name], Department of Medicine, Oslo University Hospital Aker.

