### **Alternative hypotheses:**

Duodenal switch leads to a 10-20% greater weight loss (after two years) than does gastric bypass.

Weight regain from two years after surgery is greater after gastric bypass than after duodenal switch.

Duodenal switch patients experience more gastrointestinal side effects than does patients after gastric bypass.

Duodenal switch patients experience more nutritional disorders.

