### **4. Methods**

#### **Study design:**

Two-center, prospective, randomized trial.

Relevant parameters are registered prospectively in designated form (Case Record Form).

Each patient is his own control regarding the above-mentioned end points.

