#### **Analytical methods:**

*Weight loss evaluated before and 1½, 6, 12, 24 and 60 months after surgery:*

Weight, BMI, and percentage weight lost.

*Body composition evaluated before and 12 and 24 months after surgery:*

Waist and hip circumferences and sagittal abdominal diameter.

Segmental bioelectrical impedance analysis in Norwegian participants. 40K spectroscopy in Swedish participants.

*Quality of life evaluated by the following questionnaires before and 12, 24 and 60 months after surgery:*

Short Form 36 health survey (SF-36).

The Obesity-related problems scale (OP-scale).

Gastrointestinal quality of life (GSRS).

Questionnaire on bowel function ("Frågeformulär tarmfunktion").

*Eating pattern (measured at similar time points):*

Three factor eating questionnaire (TFEQ).

Four-day dietary record.

Additional questions about diet and supplements.

*Health economics:*

The use of disposable surgical equipment.

Lengths of surgery and anesthesia.

Lengths of stay in post-operative department and in intensive care unit.

Length of hospital stay (expenses are converted into costs in NOK or Euros by current method applied at Sahlgrenska).

Number of visits in primary care and outpatient clinics because of obesity - before and after surgery.

*Associated diseases evaluated before and 12, 24 and 60 months after surgery:*

Diabetes: Measurement of fasting plasma glucose and insulin and record of any use of antidiabetic drugs.

Hypertension: Measurement of blood pressure and the need for medication.

Dyslipidemia: Measurement of lipids and the need for medication.

*Complications:*

Recording of early complications (within 30 days after surgery) such as anastomotic leak, hemorrhage demanding surgical intervention, pulmonary embolism, abscess, reoperations, and death etc. Further registration of late (>30-day) complications at outpatient visits.

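### A clinic nutritionist guides patients through the quality-of-life and eating questionnaires, with no blinding, neutral script or unaided completion described

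*Protocol*

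**What the plan says.** Section 5 of the protocol is headed as applying to the Norwegian part of the study. At the first consultation the patient is "examined by a physician, research nurse and nutritionist". The section then sets the questionnaire procedure: "The nutritionist will be responsible for informing and guiding the patient by filling in the questionnaires regarding quality of life and eating patterns". For follow-up it says: "At outpatient visits, data registration is performed by physician and nutritionist".

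The end points concerned are named in section 2: "Secondary end points: Long-term results regarding quality of eating and quality of life". Section 4, under Analytical methods, gives the timing: "Quality of life evaluated by the following questionnaires before and 12, 24 and 60 months after surgery". The instruments listed there are SF-36, the OP-scale, GSRS and a bowel-function questionnaire. TFEQ, a four-day dietary record and additional questions on diet and supplements follow at similar time points.

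The design statement in section 4 is "Two-center, prospective, randomized trial". The protocol uses neither the term blinded nor the term open label, and it names no independent assessor.

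Among the alternative hypotheses is: "Duodenal switch patients experience more gastrointestinal side effects than does patients after gastric bypass". More nutritional disorders are also expected after duodenal switch. For quality of life and quality of eating, only similarity between the groups is hypothesised.

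**The concern.** SF-36, the OP-scale, GSRS, the bowel-function questionnaire and TFEQ are answered by the patient. After surgery, a member of the clinic staff who guides the answers probably knows which operation was done. That person can affect the answers by explaining items, by prompting, or simply by being present. If this happens differently in the two arms, the resulting shift is part of the between-group difference, and no later analysis can separate it from a treatment effect.

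The concern is sharpest where a written expectation and a guided questionnaire bear on the same outcome. That is the case for gastrointestinal symptoms, which GSRS and the bowel-function questionnaire measure directly. Several named secondary end points are at stake. Weight is not.

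**Working it through.** **The plan's own figure.** The only power statement in the protocol concerns change in BMI. The planning values are 24.9 (SD 5.0) and 18.0 (SD 6.7), a difference of 6.9. The root-mean-square SD is √((5.0² + 6.7²)/2) = 5.91. With 60 participants and 30 per arm assumed, since the allocation ratio is not stated, the standard error is 5.91 × √(2/30) = 1.526. The ratio is 6.9/1.526 = 4.52, which gives power of about 99%. The stated figure of more than 90% is therefore met. It has no bearing on the questionnaires.

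**What the text establishes, step by step.**

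1. *Guidance by clinic staff:* stated. The nutritionist is one of the three staff members who see the patient at the first consultation.
2. *Guidance at follow-up:* not stated, but not excluded. The sentence comes after the account of the first consultation and the preoperative forms, yet it carries no limit to baseline. The instruments are repeated at 12, 24 and 60 months, and the nutritionist is named for data registration at outpatient visits. If only baseline was meant, the protocol does not say how the questionnaires are given after surgery.
3. *Knowledge of the operation:* inferred. The two operations differ, clinic staff follow the patient and record late complications, and nothing is described that would keep them unaware.
4. *A neutral procedure:* not described. Section 5 standardises the information on postoperative diet but says nothing comparable about help with the questionnaires.
5. *Expected direction:* written for gastrointestinal side effects and nutritional disorders, but not for quality of life or quality of eating. The Background section even mentions possibly better eating after duodenal switch, so no single expectation covers all the scores.

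**Illustration of size.** The shifts below are assumed; the protocol gives no basis for choosing among them. With 30 per arm, the standard error of a standardised difference is √(1/30 + 1/30) = 0.258 SD. With no true difference and a between-arm shift of b SD, the two-sided 5% false-positive rate is Φ(−1.96 + b/0.258) + Φ(−1.96 − b/0.258).

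| Assumed shift b, all patients | b/0.258 | False-positive rate |
|---|---|---|
| 0 | 0 | 5.0% |
| 0.10 SD | 0.387 | 6.7% |
| 0.25 SD | 0.968 | 16.2% |

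The rule is written for Norway only. Suppose that half of each arm were Norwegian (the split is not given) and that Swedish answers were not shifted. The pooled shifts would then be 0.05 and 0.125 SD, the ratios 0.194 and 0.484, and the rates about 5.4% and 7.7%.

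**The case against.** The strongest reply is that the guidance sentence stands among preoperative tasks and may describe baseline only, where the operation has not yet been done and cannot affect the answers. The follow-up sentence speaks of registering data, not of guiding answers. Informing and guiding may also mean no more than neutral instruction on how to complete a form, and such detail often sits in a working manual. This stands in part: extension to follow-up is a possible reading, not a stated fact. It does not remove the point, because the protocol does prescribe a procedure for these end points and sets no boundary on it.

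A reader might infer more than the document supports:

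- **That the trial is declared unblinded, or that the nutritionist is a treating clinician who knows the allocation.** The protocol says neither. Only the physician is called treating, and knowledge of the operation is a plausible inference.
- **That all the questionnaire scores would shift in the direction the protocol expects.** A direction is written only for gastrointestinal and nutritional outcomes.
- **That the eating and gastrointestinal hypotheses rest on these questionnaires alone.** Eating is also measured by the dietary record and additional diet questions, and late complications are registered separately.
- **That the false-positive rate is greatly inflated.** A large figure follows only from assuming a large shift in all 60 patients, although the rule covers one country.
- **That the Swedish hospital does something different.** Silence does not show this, and a difference between hospitals is not in itself a difference between randomised arms.

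It is also true that patients may know their own operation, and self-completion does not change that.

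**Conclusion.** The point holds as an avoidable risk of bias in patient-reported secondary end points. It is not a demonstrated error or a contradiction. It rests on two inferences: that the guidance, or something like it, continues after surgery, and that the nutritionist then knows the operation. Both are likely under the text, and neither is stated.

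The risk is clearest for GSRS and the bowel-function questionnaire. For SF-36, the OP-scale and TFEQ it exists without a predicted direction. Neither the size nor the direction of any shift can be derived from the document. The rates of about 7% and 16% assume 30 per arm and shifts of 0.10 and 0.25 SD in all patients; they fall to about 5% and 8% if only half the patients are affected. The weight-based primary end point and its sample size are unaffected. The change is worth making because it is cheap and because a bias of this kind cannot be repaired at analysis.

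**What to change.** Amend section 5, and apply the text at both hospitals, as follows:

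- At baseline and at 12, 24 and 60 months, patients complete SF-36, the OP-scale, GSRS, the bowel-function questionnaire and TFEQ themselves, before seeing the physician or nutritionist.
- Staff give only neutral, standard written instructions and check for skipped pages. They do not discuss or enter answers.
- Staff instruction is kept for the technique of the four-day dietary record.

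This takes a few lines of text and a change in the order of the visit, with no extra staff. The downside is slightly more skipped items, or longer visits for patients with reading difficulty. Patients' own knowledge of their operation remains a limitation and should be acknowledged when these end points are reported.

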### **Time frame**

Inclusion of participants will start approximately January 2006. All data will be recorded prospectively and consecutively. Analysis and publication of the short-term results – including hospital stay and 30-day complication rates – is planned for the first half of 2007.

Long-term results (2 years) are planned for publication later than the first half of 2009.

The study will involve 5 years of follow-up.

### **6. Ethical considerations**

The study will be conducted in accordance with the Helsinki Declaration.

The study is to be approved by the regional ethics committees in both countries, and may only commence after approval is received. It is also applied for permission from The Data Inspectorate to register information on all patients treated for morbid obesity at OUH. The study has already been approved by the medical faculties at the Sahlgrenska Academy ethics committee, University of Gothenburg.

Both surgical methods have been established at the two hospitals, and are accepted methods for the treatment of super-obesity. There is no consensus on which surgical method that provides the best treatment outcome. This study aims to help clarify this and will provide new medical knowledge that is important. We see no ethical qualms about using both surgical methods.

Patients are not subjected to risks associated with additional tests or investigations solely carried out for study purposes.

Participation in the study is voluntary, and patients will be informed about the study both orally and in writing. Participants may withdraw from the study at any time without giving any reason for this.

The patients will be asked to participate in the study by the attending physician, and may as such experience some degree of pressure for participating. It must therefore be emphasized that participation in the study is voluntary.

All information obtained in the study will be treated confidentially and will only be known to the responsible employees.

## **7. Publications**

We plan to present the results in scientific papers in international peer-reviewed journals with publications for each of the collaborators involved. This applies for [name], [name], [name], and [name]. [name] already has a clear plan for his doctorate.

The research nurses may be offered co-authorships in studies regarding quality of life or in cases where they have been active in research in accordance with current regulations for authorship.

## **8. Funding (for the Norwegian part)**

All employees have a salary at the respective departments. It will be applied for financial support from South-Eastern Norway Regional Health Authority.

## **9. Insurance**

Standard patient insurance applies.

